## Methods

### Study design

The TELEGRAM-MI trial is a pragmatic, randomized controlled trial with blinded outcome assessment, initially conducted as a single-center study with a protocol structure that allows for potential multicenter expansion. Participants will be randomized in a 1 : 1 ratio to the intervention or control group. The trial will be conducted in inpatient cardiology departments at the Ulyanovsk Regional Clinical Hospital. The pragmatic design aims to assess the intervention’s effectiveness in real-world clinical practice. The protocol was approved by the Local Ethics Committee of the clinical center (Ulyanovsk regional hospital, #PN0104122025, 04.12.2025) and registered on ClinicalTrials.gov (NCT07230249). Written informed consent will be obtained from all participants.

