### Outcomes and assessments

#### Primary outcome

The primary outcome will be 30 day point prevalence abstinence (PPA) at 6 months, defined as self-reported non-smoking via bot for the preceding 30 days corroborated by a relative/cohabitant report during a blinded telephone interview. Participants with missing data or data not corroborated by a relative after two attempts will be considered smoking.

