### Sample size calculation

Assuming 6 month abstinence rates of 10% (control)^4^ and 30% (intervention), 120 participants (60/group) are needed for 80% power with a two-sided alpha of 0.05. Allowing for a 15% dropout rate, the target sample size is 142 (71/group). The assumptions are based on prior evidence, where abstinence after brief advice is around 10%^9^, and a larger effect is considered plausible due to the acute motivational impact of myocardial infarction^11^.

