### Statistical analysis

Analyses will follow the intention-to-treat principle, with participants lost to follow-up considered smokers for the primary outcome. Baseline characteristics will be presented descriptively in Table 2^6^. The primary analysis will compare 6 month abstinence rates using a chi-squared test, reporting absolute risk difference and relative risk (RR) with 95% confidence intervals (CIs). Continuous outcomes will be analyzed using linear mixed models. Time to first relapse will be analyzed with Kaplan-Meier curves and Cox regression. Exploratory analyses will use logistic regression to assess associations between baseline factors, engagement, and cessation. A per-protocol secondary analysis will include intervention-group participants who completed ≥60% of weekly check-ins during the first 3 months and had their final assessment within 6 months±3 weeks; this criterion does not apply to the control group.

**Table 2 T2:** Baseline demographic and clinical characteristics of TELEGRAM-MI participants by trial arm (template for future Table)

Characteristics	Total	Intervention	Control

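### The secondary per-protocol analysis selects only the intervention arm, on behaviour after randomisation, and is likely to overstate the bot's effect

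*Protocol article*

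**What the plan says.** The Statistical analysis section makes intention-to-treat the governing principle and counts participants lost to follow-up as smokers for the primary outcome. It then adds: "A per-protocol secondary analysis will include intervention-group participants who completed ≥60% of weekly check-ins during the first 3 months". A second condition requires the last assessment to fall no more than three weeks either side of month 6. The sentence closes with an exemption: "this criterion does not apply to the control group". So there are two conditions for the intervention arm, followed by an exemption for controls. Because the exemption names the control group, a comparison between arms is evidently intended.

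Three other places bear on this:

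- Primary outcome: "Participants with missing data or data not corroborated by a relative after two attempts will be considered smoking".
- Secondary outcomes: missing data there are handled on available cases. Table 1 records time to first relapse through the weekly check-ins.
- Interventions: the control bot serves only for assessments at baseline and at 1, 3 and 6 months. No weekly check-in is described for controls, so they cannot be filtered in the same way.

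**The concern.** A per-protocol comparison keeps the protection of randomisation only so far as the same selection acts on both arms. Here one arm is selected on behaviour after randomisation and the other is not.

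Two separate distortions can follow.

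- **Check-in selection.** Answering weekly check-ins is not a neutral measure of dose. It is the channel through which lapses and relapse are reported. If people who resume smoking tend to stop answering, the 60% rule keeps abstainers and sheds smokers in the intervention arm alone.
- **Denominator.** If controls are also exempt from the on-time assessment, and missing controls count as smokers, then missing participants leave the denominator in one arm and stay in it in the other.

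At stake is a secondary result that could be read as the effect of using the bot properly, when part or all of the difference comes from who was kept.

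**Working it through.** **Inputs from the protocol article.** Control abstinence comes from "Assuming 6 month abstinence rates of 10% (control") and arm size from "Allowing for a 15% dropout rate, the target sample size is 142 (71/group"). Loss is 15%. Allocation is 1:1 and the test is a chi-squared test at two-sided 0.05.

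**Plan's own figure.** The per-protocol analysis has no stated figure to reproduce, but the arm size can be checked. For 10% against 30%, the unpooled normal formula gives (1.960 + 0.842)² × (0.09 + 0.21) / 0.04 = 58.9 per group. The arcsine formula gives 59.01, rounded up to 60, and the pooled formula gives 62. The stated 60 is reproduced, and 60 / 0.85 = 70.6, rounded up to 71.

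**Assumptions not in the document.** The bot has no effect. Confirmed abstinence is p in both arms. Everyone lost is a smoker. A share a of abstainers and a share s of observed smokers meet the 60% rule.

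**Formula.** With loss d, the abstinence rate in the intervention per-protocol set is

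p·a / [p·a + (1 − d − p)·s]

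The control rate is p if all controls are kept with missing counted as smoking, and p / (1 − d) if only controls with a completed assessment are kept.

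**Step 1: denominator alone.** Set a = s, so check-ins are unrelated to abstinence, with p = 0.10 and d = 0.15. The intervention rate is 0.10 / 0.85 = 11.8%. Against all controls (10.0%) the relative risk is 1.18. Against controls who completed (0.10 / 0.85 = 11.8%) the difference is zero.

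**Step 2: adding check-in selection, p = 0.10.**

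- 80% against 60%, no loss: 0.08 / (0.08 + 0.54) = 12.9%. With 15% loss: 0.08 / (0.08 + 0.45) = 15.1%.
- 90% against 50%, no loss: 0.09 / (0.09 + 0.45) = 16.7%. With 15% loss: 0.09 / (0.09 + 0.375) = 19.4%.
- 80% against 40%, no loss: 0.08 / (0.08 + 0.36) = 18.2%. With 15% loss: 0.08 / (0.08 + 0.30) = 21.1%.
- 50% against 70% (abstainers check in less), with 15% loss: 0.05 / (0.05 + 0.525) = 8.7%.

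**Step 3: chance of a significant result favouring the bot.** Simulation of 400,000 trials per case, 71 per arm, uncorrected chi-squared test. With no selection in either arm it returns the nominal 2.5%.

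| Adherent: abstainers / smokers | No loss (control 10.0%) | 15% loss, all controls kept (control 10.0%) | 15% loss, completers only in both arms (control 11.8%) |
|---|---|---|---|
| 80% / 60% | 7.7% | 13.4% | 7.7% |
| 90% / 50% | 18.5% | 27.8% | 18.2% |
| 80% / 40% | 22.9% | 32.3% | 22.1% |
| 50% / 70% | 0.8% | 1.7% | 0.8% |

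The last column shows that applying the completion rule to both arms removes the denominator part but not the check-in part. At 90% against 50%, 19.4% − 11.8% = 7.6 points remain with no true effect.

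**The case against.** Several points on the other side stand.

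- **The analysis is secondary.** It does not touch the primary test, risk difference or relative risk, and nothing in the protocol makes a success claim depend on it.
- **The direction is not certain.** A reader might infer that the analysis must produce a spurious benefit. The document gives no adherence by outcome. The Interventions section describes more outreach after a reported lapse or high craving, which could keep lapsers responding. If abstainers checked in less than smokers, the bias would reverse.
- **The exemption is ambiguous.** A reader might infer that controls face neither condition. But "this criterion does not apply to the control group" is in the singular after two conditions, and it may exempt controls only from check-ins, which they are not described as having. The assessment window could then bind both arms.
- **The missing-data rule for this set is not stated.** Counting missing as smoking is tied to the primary outcome, while secondary outcomes use available cases. That missing controls stay in and count as smokers is one reading, not a stated fact.
- **Larger figures need a different base rate.** At 20% abstinence the false-benefit rates are higher, but the protocol assumes 10% in controls.

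None of this removes the check-in selection. It is explicit for one arm, has no counterpart in the other, and no adjustment is stated.

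**Conclusion.** The concern holds in a limited form. The check-in filter acts on one arm only, so the per-protocol contrast is open to selection bias. It is likely to exceed the intention-to-treat effect if relapsers answer less often.

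At the protocol's 10% abstinence and 71 per arm, a bot without effect would show a significant benefit in roughly 8% to 13% of trials (80% against 60% adherent), 18% to 28% (90% against 50%) or 22% to 32% (80% against 40%), against a nominal 2.5%. The adherence shares are assumed. The span within each pair reflects loss and the handling of missing controls.

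The further denominator effect (11.8% against 10.0%, relative risk 1.18) arises only if controls are exempt from the assessment window and missing controls count as smokers.

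The document does not support the stronger conclusions that a spurious benefit is certain or that the main result is compromised. This should be fixed, and it leaves the primary analysis intact.

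**What to change.** 1. State that the window of 6 months ± 3 weeks and the missing-data rule apply identically to both arms, and say which missing-data rule governs this analysis.
2. Drop the between-arm test of the subgroup with at least 60% of check-ins. Report that subgroup descriptively within the intervention arm, labelled exploratory and non-causal. Step 1 alone would not be enough, as the last column of the table shows.
3. If an effect of adherence is wanted, a complier-average estimate with randomisation as the instrument may be added as exploratory. It divides the intention-to-treat risk difference by the adherent proportion, and so assumes no effect in participants below 60%. That is doubtful, because they still receive bot messages, and the estimate may be too large. For example, suppose effects of 20 points in adherers and 10 in the rest, with half adherent. The intention-to-treat difference is 0.5 × 20 + 0.5 × 10 = 15 points, and 15 / 0.5 = 30 points exceeds both. The assumption must be stated with the result.

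The cost is wording and a few lines of code, with no new data. The change should be made before outcomes are seen. The downside is a less favourable-looking secondary result.

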**Sociodemographic**			
Age (years), mean (SD)			
Age≥65 years, n (%)			
Male, n (%)			
**Smoking-related**			
Cigarettes per day, mean (SD)			
Years of smoking, mean (SD)			
FTND score (0–10), mean (SD)			
FTND≥6 (high dependence), n (%)			
Previous quit attempts (past year), n (%)			
Motivation to quit^a^, mean (SD)			
**Technology use**			
Daily Telegram use, n (%)			

a Prochaska questionnaire (0–6)

FTND: Fagerström test for nicotine dependence.

### Data management

Data will be stored on a secure, encrypted server. Because the Telegram bot interacts with participants via usernames rather than accessing personal phone numbers, the primary dataset is inherently pseudonymized. Identifiable data will be kept separate in a password-protected file with restricted access. No formal Data Monitoring Committee is planned due to low risk. Interim analyses are not planned.

## Discussion

Although several tobacco cessation apps and chatbots already exist, none is designed for the specific needs of MI survivors, a group for whom smoking cessation is often driven not by personal readiness but by the acute medical crisis and forced withdrawal during hospitalization^9^. This population requires sustained, structured support after discharge, yet most existing digital tools operate independently of healthcare systems and are not integrated into routine cardiac follow-up^9^. A key innovation of the TELEGRAM-MI trial is that it tests a model in which hospitals themselves can remotely support patients using a low-cost digital tool built on a widely used social messaging platform. Unlike commercial apps, a Telegram-based chatbot can be developed, deployed, and maintained directly by clinical teams without collecting sensitive personal data, making it feasible for public hospitals with limited technical infrastructure. To our knowledge, no trial has evaluated a messenger-based automated support program specifically for post-MI patients or explored whether a hospital-operated chatbot can extend secondary prevention beyond the hospital walls. This approach represents a novel direction for digital cardiac rehabilitation and offers a scalable strategy for long-term tobacco cessation support in high-risk patients.

### Strengths and limitations

This trial has several key strengths. First, its pragmatic design embeds the intervention within routine cardiology care, enhancing the real-world applicability and scalability of findings. Second, the use of a widely adopted messaging platform in this country (Telegram) minimizes barriers to participant training and leverages a familiar technology to sustain engagement. Third, the methodology incorporates blinded outcome assessment with external verification (relative report), reducing detection bias for the primary endpoint.

Several limitations must be acknowledged. The primary reliance on self-reported abstinence, despite external verification, is subject to potential social desirability bias in the absence of biochemical validation (e.g. cotinine testing). This methodological choice was guided by the pragmatic, remote nature of the trial to maximize follow-up rates and reduce participant burden. Second, the eligibility criterion requiring Telegram use excludes smokers who do not use this platform or smartphones, which may limit the generalizability of the results to the entire post-MI smoking population and could introduce selection bias, potentially excluding people with lower levels of education and income. Third, the initial single-center recruitment may limit the geographical and clinical diversity of the sample, although the protocol allows for multicenter expansion. Additionally, exclusion of other tobacco products limits the generalizability of the findings.

## Conclusions

If effective, this intervention offers a scalable, low-cost model for integrating behavioral support into cardiac rehabilitation in resource-constrained settings. It may also provide sustained cessation support beyond the brief quit advice given in hospital and help shape national cessation strategies by showing whether a simple digital tool can improve quit rates in a high-risk group. Future research should focus on implementation studies, trials with biochemical validation, adaptation to other risk factors, and use in other chronic conditions such as COPD or diabetes. Protocol version 1.0 is dated 27 October 2025. Recruitment is planned to commence in January 2026, with primary completion (final follow-up at 6 months) estimated for October 2026.
